### Overview

This RCT consists of three study arms (see Figure 1). Study coordinators tell prospective participants about the availability of genetic testing for diabetes risk, and ask them if they would be interested in undergoing such testing as part of a research study. After providing informed consent to participate and having eligibility confirmed, those interested in genetic testing are randomly assigned to undergo *either *a standard risk assessment (SRA) for type 2 diabetes plus upfront disclosure of the results of genetic risk testing (SRA+G), *or *the SRA alone (SRA). (The standard SRA incorporates the conventional risk factors of fasting glucose, body mass index (BMI), race/ethnicity, and age.) Patients not interested in genetic testing for diabetes risk are not randomized and receive only the SRA in a third study arm (No-Test).

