### Study measures: Outcomes

Primary clinical outcomes are changes in insulin resistance and weight over 12 months. Change in insulin resistance will be assessed by measuring fasting insulin and serum glucose levels at baseline and 12 months, and calculating the homeostasis model assessment of insulin resistance (HOMA-IR). The HOMA-IR is a widely-used measure of insulin resistance that is tightly correlated with the criterion standard of direct measurement by insulin clamp technique [29,30]. Change in weight will only be analyzed among overweight and obese patients (because healthy-weight patients will presumably not be counseled to lose weight). Weight at 12 months will control for baseline weight; specifically, the 12-month weight outcome variable will be residualized change scores (residuals captured from regressing 12-month weight onto baseline weight).

Secondary clinical outcome measures will be changes in diet, energy expenditure, and waist circumference. Change in diet will be measured using the 16-item dietary subscale from the National Health Interview Survey [31] and change in energy expenditure is measured using the World Health Organization's (WHO) Global Physical Activity Questionnaire [32]. Waist circumference will be measured at baseline and 12 months; the waist is defined as the midpoint between the highest point of the iliac crest and the lowest point of the costal margin at the midaxillary line [33]. All 3-month and 12-month outcome variables will be residualized change scores.

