### Analyses

Data will be analyzed according to intention-to-treat principles. Data will be checked for completeness and the characteristics and frequency of missing data will be described. Missing data values will be imputed as appropriate.

Our primary hypothesis is that patients in the SRA+G arm will have a greater reduction in insulin resistance and lose a greater percentage of their baseline weight after 12 months compared to patients in the SRA arm. We will test these hypotheses with linear multiple regression models with weight or insulin resistance at 12 months as the outcomes (testing a separate model for each outcome) and arm, clinic site, and baseline patient characteristics as explanatory and control variables. We will test our hypothesized mechanism with mediation analysis; specifically, hierarchical linear regression models will test whether effects of the intervention on insulin resistance and weight at 12 months is partially or fully accounted for by perceived risk at 3 months.

Our secondary hypotheses are that patients in the SRA+G group will report significantly healthier dietary changes and will have significantly greater average weekly energy expenditure than patients in the SRA group after 3 months. We will test this hypothesis with linear multiple regression models with behavioral variables at 3 months as the outcomes (testing a separate model for each variable) and arm, clinic site, and baseline patient characteristics as explanatory and control variables. We predict that this difference will narrow, but will still be significant at 12 months; we will test this hypothesis by fitting the same regression model with 12-month behavioral variables as outcomes. In addition, we hypothesize that overweight and obese patients in the SRA+G group, irrespective of diabetes genetic panel test result, will have a greater reduction in waist circumference. Residualized change scores (controlling for baseline values) will be used for 3- and 12-month outcome variables.

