We will analyze the roles of process variables using moderation analyses in linear regression models. We predict (1) that patients who believe genetics plays a greater role in their risk of type 2 diabetes will be more likely to improve diet and exercise behavior at 3 months than those who believe genetics plays a lesser role in their diabetes risk; (2) that patients with higher perceived personal risk for Type 2 diabetes - regardless of actual test results, and regardless of group assignment - will be more likely to improve diet and exercise behavior at 3 months; (3) that patients with more positive affective responses (e.g., not anxious, guilty, or fearful) and more concern about their risk for type 2 diabetes - regardless of actual test results, and regardless of group assignment - will be more likely to improve diet and exercise behavior at 3 months; and (4) that patients with higher perceived control over their risk for type 2 diabetes will be more likely to maintain dietary and exercise behavior changes at 12 months.

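### Residualising outcomes on baseline before the regression leaves the randomised comparison essentially intact, but understates mediation if perceived risk correlates with baseline; a one-step model avoids this

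*Protocol article*

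**What the plan says.** Under Study measures: Outcomes, the protocol article defines the 12-month weight outcome as "residuals captured from regressing 12-month weight onto baseline weight" and extends the device to everything else: "All 3-month and 12-month outcome variables will be residualized change scores". The Analyses section repeats it: "Residualized change scores (controlling for baseline values) will be used for 3- and 12-month outcome variables".

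The second step, in Analyses, is linear multiple regression with "arm, clinic site, and baseline patient characteristics as explanatory and control variables". Mediation is tested by asking whether the intervention effect on insulin resistance and weight "is partially or fully accounted for by perceived risk at 3 months". For the remaining survey constructs the article says: "We will analyze the roles of process variables using moderation analyses in linear regression models". Those models concern diet and exercise behaviour.

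The second-step covariate list does not name the baseline value of the outcome. It may or may not fall within the baseline patient characteristics.

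**The concern.** Residualising takes the baseline value out of the outcome only. The second-step regressors still carry whatever they share with baseline. In ordinary covariate adjustment baseline is removed from both sides, and the two procedures agree only when the regressor is uncorrelated with baseline.

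For a randomised arm that holds apart from chance. For perceived risk at 3 months it probably does not. The Risk profiling section has every participant counselled from a profile that colour-codes their own BMI and fasting glucose. Weight is a primary outcome, and HOMA-IR is computed from fasting glucose and insulin. Some correlation between later perceived risk and these baseline values is therefore plausible.

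At stake is the test of the trial's hypothesised mechanism. The mediator coefficient would be too small and the direct arm effect too large, and both errors make mediation look weaker than it is.

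**Working it through.** **Inputs from the article (Power and sample size considerations).** Weight: difference 2/3 of 1.7%, SD 3.9, 198 per group. HOMA-IR: difference 0.5, SD 2.0, 253 per group. Two-sided 0.05 (sidedness stated for weight, assumed for HOMA-IR), 80% power. The article gives no figure for the bias; these inputs only set N. Allocation is assumed 1:1 and dropout is ignored.

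**Reproducing the sample sizes.** n = 2(1.96 + 0.8416)² SD²/difference².
- Weight, with the difference rounded to 1.1: 15.70 × 15.21/1.21 = 197.3, so 198.
- HOMA-IR: 15.70 × 4/0.25 = 251.2, so 252, or 253 with the t distribution.

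Totals are N = 396 and N = 506.

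**The identity.** For a regressor A and baseline x, when no other regressor is correlated with x, two-step coefficient = one-step coefficient × (1 - r²), where r is the correlation of A with x.

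**Randomised arm.** By chance alone the expected r² is 1/(N - 1).
- N = 506: 1/505 = 0.2%.
- N = 396: 1/395 = 0.25%.
- Chance baseline imbalance of d SD: r² = (d/2)²/(1 + (d/2)²). For d = 0.2 this is 0.01/1.01 = 1.0%; for d = 0.3 it is 0.0225/1.0225 = 2.2%.

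Simulation (8,000 runs, with a covariate correlated 0.5 with baseline):

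| Outcome | Arm effect, two-step / one-step | Power | Type I error |
|---|---|---|---|
| HOMA-IR, N = 506 | 0.4976 / 0.4983 | 0.797 / 0.796 | 0.049 / 0.050 |
| Weight, N = 396 | 1.104 / 1.106 | 0.798 / 0.797 | 0.047 / 0.047 |

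**Mediator, no other correlated covariate (r assumed).** 1 - r² gives 0.96, 0.91, 0.84 and 0.75 at r = 0.2, 0.3, 0.4 and 0.5, that is 4%, 9%, 16% and 25% shrinkage. Simulation at N = 400 gave ratios of 0.958, 0.908, 0.838 and 0.749.

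**Effect on the mediation split.** Simulated at N = 506, with assumed values: mediator coefficient 0.60, arm effect on the mediator 0.4, direct arm effect 0.50. The total effect is 0.50 + 0.4 × 0.60 = 0.74.

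| r | Mediator, two-step / one-step | Direct arm effect, two-step / one-step |
|---|---|---|
| 0.3 | 0.544 / 0.598 | 0.520 / 0.500 |
| 0.5 | 0.449 / 0.599 | 0.559 / 0.499 |

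Arithmetic agrees: 0.74 - 0.24 × 0.91 = 0.522 and 0.74 - 0.24 × 0.75 = 0.560. The total is preserved, so what the mediator loses moves into the direct effect. The mediated share falls from 0.24/0.74 = 32% to 0.218/0.74 = 30% at r = 0.3 and 0.18/0.74 = 24% at r = 0.5.

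**Mediator with a baseline proxy in the model.** Suppose a covariate such as BMI correlates p with baseline, perceived risk correlates r with both, and the proxy has no effect of its own once baseline is known. The proportional shrinkage is then r²(1 - p)/(1 - r²).

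| r | p = 0.85 | p = 0.7 |
|---|---|---|
| 0.2 | 0.04 × 0.15/0.96 = 0.6% | 0.04 × 0.3/0.96 = 1.3% |
| 0.3 | 0.09 × 0.15/0.91 = 1.5% | 0.09 × 0.3/0.91 = 3.0% |
| 0.4 | 0.16 × 0.15/0.84 = 2.9% | 0.16 × 0.3/0.84 = 5.7% |
| 0.5 | 0.25 × 0.15/0.75 = 5.0% | 0.25 × 0.3/0.75 = 10.0% |

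Simulation for r = 0.3 to 0.5 gave the same values to rounding.

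**Baseline value itself in the second step.** The two-step and one-step arm coefficients were then identical in simulation (difference 0.0000). The residualising step does nothing.

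**The case against.** A reader might infer that every coefficient, including the primary treatment effect, is pulled toward zero. The documents do not support that. Participants interested in testing are randomised between the two arms compared, so the arm correlates with baseline only by chance, and power and type I error do not move. Nor is the direction general: in the mediation model the direct arm effect moves away from zero.

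Other points on that side:

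- **The correlations are assumed.** This stands. Restricting the weight analysis to overweight and obese patients narrows the range and argues against the high end. Insulin is not among the items the article lists for the profile, so any link between perceived risk and HOMA-IR is partly indirect. Fasting glucose and BMI are shown, however, so a zero correlation would be surprising.
- **Baseline may already be in the second step.** The article condenses a fuller document, and its covariate wording leaves this open. If baseline is included, the bias is zero. Against this, the Analyses section describes the residualised scores as themselves controlling for baseline, which suggests that nothing further is planned.
- **The test suffers less than the coefficient.** This stands. The standard error shrinks too, so the t statistic falls only by about the square root of 1 - r². Simulated t ratios at r = 0.3, 0.4 and 0.5 were 0.95, 0.91 and 0.86, and 0.99, 0.98 and 0.96 with a 0.85 proxy.
- **The process models rest on other baselines.** This stands. They concern diet and exercise, so only correlation with baseline diet or activity matters. The article gives no reason to expect a particular size.
- **Covariate coefficients are also shrunk.** True but of no consequence, since no hypothesis concerns them.

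**Conclusion.** The point holds in a limited form centred on the mediation analysis. The two-step method is stated plainly, so this is a choice of method and not a missing detail. For the primary and secondary arm comparisons the effect is negligible.

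In the mediation model the mechanism is understated to a degree that depends on unknowns: about 4-25% shrinkage of the perceived-risk coefficient for r of 0.2 to 0.5 with no other correlated covariate, about 1-10% with a proxy correlated 0.7-0.85 with baseline, and none if the baseline value is adjusted for. The direct arm effect is overstated correspondingly, provided the arm shifts perceived risk and perceived risk shifts the outcome in the hypothesised directions.

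The figures rest on assumed correlations, 1:1 allocation and no dropout. The process models are exposed only so far as their predictors correlate with baseline diet or activity.

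**What to change.** In Study measures: Outcomes and in Analyses, replace the residualising step with a single linear regression of each 3- or 12-month outcome on arm, clinic site, the baseline value of that outcome and the other baseline covariates. Use the same one-step form for the mediation models (adding perceived risk at 3 months) and for the process-variable models.

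If the baseline value was always meant to be a second-step covariate, say so and drop the residuals, which then serve no purpose.

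The cost is a change of wording and one degree of freedom per model, with the same data and software and no material loss of power. Whether the weight outcome is weight or percent weight change is a separate issue that this change does not settle.

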### Process Measures

Surveys will assess several process variables at several time points. *Belief in the role of genetics in type 2 diabetes risk *and *perceived personal risk for type 2 diabetes *are measured with newly designed items based on Common Sense principles. *Affective response to diabetes risk *are measured with the Consequences subscale of the Brief Illness Perception Questionnaire [34] and the Multidimensional Impact of Cancer Risk Assessment (MICRA) Questionnaire [35], both adapted to type 2 diabetes. *Perceived control over risk for type 2 diabetes *is measured with the personal control subscale of the Brief IPQ (adapted for type 2 diabetes).

### Analyses

Data will be analyzed according to intention-to-treat principles. Data will be checked for completeness and the characteristics and frequency of missing data will be described. Missing data values will be imputed as appropriate.

Our primary hypothesis is that patients in the SRA+G arm will have a greater reduction in insulin resistance and lose a greater percentage of their baseline weight after 12 months compared to patients in the SRA arm. We will test these hypotheses with linear multiple regression models with weight or insulin resistance at 12 months as the outcomes (testing a separate model for each outcome) and arm, clinic site, and baseline patient characteristics as explanatory and control variables. We will test our hypothesized mechanism with mediation analysis; specifically, hierarchical linear regression models will test whether effects of the intervention on insulin resistance and weight at 12 months is partially or fully accounted for by perceived risk at 3 months.

Our secondary hypotheses are that patients in the SRA+G group will report significantly healthier dietary changes and will have significantly greater average weekly energy expenditure than patients in the SRA group after 3 months. We will test this hypothesis with linear multiple regression models with behavioral variables at 3 months as the outcomes (testing a separate model for each variable) and arm, clinic site, and baseline patient characteristics as explanatory and control variables. We predict that this difference will narrow, but will still be significant at 12 months; we will test this hypothesis by fitting the same regression model with 12-month behavioral variables as outcomes. In addition, we hypothesize that overweight and obese patients in the SRA+G group, irrespective of diabetes genetic panel test result, will have a greater reduction in waist circumference. Residualized change scores (controlling for baseline values) will be used for 3- and 12-month outcome variables.

We will analyze the roles of process variables using moderation analyses in linear regression models. We predict (1) that patients who believe genetics plays a greater role in their risk of type 2 diabetes will be more likely to improve diet and exercise behavior at 3 months than those who believe genetics plays a lesser role in their diabetes risk; (2) that patients with higher perceived personal risk for Type 2 diabetes - regardless of actual test results, and regardless of group assignment - will be more likely to improve diet and exercise behavior at 3 months; (3) that patients with more positive affective responses (e.g., not anxious, guilty, or fearful) and more concern about their risk for type 2 diabetes - regardless of actual test results, and regardless of group assignment - will be more likely to improve diet and exercise behavior at 3 months; and (4) that patients with higher perceived control over their risk for type 2 diabetes will be more likely to maintain dietary and exercise behavior changes at 12 months.

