### Power and sample size considerations

Power and sample size estimates are based on the primary study outcomes, percent weight change (from baseline) and change in HOMA-IR, both after 12 months. Based on two studies of low-intensity clinic-based weight loss interventions, we estimate that approximately 20% of patients in the SRA+G arm will lose 5% of their body weight over the course of a year, compared to approximately 10% of patients in the SRA arm [36,37]. Under these assumptions, the mean weight change for participants in the SRA+G arm is estimated to be around 1.7% of baseline body weight, with a standard deviation of approximately 3.9; and the mean weight change to be zero in the SRA arm. We further assume that changes in weight follow normal distributions with equal standard deviations for both groups. Because we are studying a low-intensity informational intervention, for purposes of sample size calculation we will aim for sufficient power to detect a difference in weight change that is 2/3 of the 1.7% difference estimated above. Thus, approximately 198 patients are needed in each group for a two-sided type I error rate of 0.05 and 80% power.

From a number of comparable studies, we conservatively estimate that participants in the SRA+G arm will be able to lower HOMA-IR by 0.5 over the course of a year through lifestyle changes; those in the SRA arm are again assumed to have a mean change of zero. Mean baseline HOMA-IR is estimated to be 2.5 with a standard deviation near 2.0 [38-41]. Using these estimates, 253 patients per group would be required to achieve a significance level of 0.05 with 80% power.

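### Two primary outcomes are each sized at a full 0.05 with 80% power, but no rule says whether one or both must succeed, so the error rate or the power of the primary claim differs from those figures

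*Protocol article*

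**What the plan says.** Under Study measures: Outcomes, the article says: "Primary clinical outcomes are changes in insulin resistance and weight over 12 months". The Overview names the same two.

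The Analyses section gives a single primary hypothesis about the group receiving genetic results, which, it predicts, "will have a greater reduction in insulin resistance and lose a greater percentage of their baseline weight after 12 months"; the comparator is the SRA arm. The next sentence treats this as more than one hypothesis: "We will test these hypotheses with linear multiple regression models with weight or insulin resistance at 12 months as the outcomes", with the parenthesis "testing a separate model for each outcome". It gives no order of testing, division of alpha or statement of whether one or both results are needed.

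Power and sample size considerations sizes the outcomes one at a time. For weight, "approximately 198 patients are needed in each group for a two-sided type I error rate of 0.05 and 80% power". For HOMA-IR, "253 patients per group would be required to achieve a significance level of 0.05 with 80% power".

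**The concern.** A primary claim resting on two tests needs a rule that turns two p-values into one conclusion. The article has two tests at full alpha and no such rule, and its wording supports both readings: *and* in the hypothesis suggests that both are required, while the plural and the separate models suggest that each stands alone.

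The choice matters most if one outcome is significant and the other is not. That result could be reported as success or as failure, and nothing in the article settles which before the data are seen. Each reading also has a cost that the sample-size section does not show: one raises the error rate of the primary claim above 0.05, and the other lowers its power below 80%.

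**Working it through.** **Inputs from Power and sample size considerations**
- Weight: the target is "a difference in weight change that is 2/3 of the 1.7% difference estimated above", "with a standard deviation of approximately 3.9", assumed equal in both arms; two-sided 0.05, 80% power.
- HOMA-IR: difference 0.5, SD 2.0, 0.05, 80% power. Sidedness is not written for this outcome.
- Assumed here: 1:1 allocation, and a correlation ρ between the two test statistics. The article gives no ρ, so a range is shown.

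**Step 1. Reproduce the stated sizes**

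n per group = 2(z₁₋α/₂ + z₁₋β)² (SD/δ)², with (1.960 + 0.842)² ≈ 7.85.
- HOMA-IR: 2 × 7.85 × (2.0/0.5)² ≈ 251.2, so 252 by the normal approximation and 253 by the t test. A one-sided test would need only 198, so 253 implies two-sided testing.
- Weight: 2/3 × 1.7 = 1.133. Rounded to 1.1, 2 × 7.85 × (3.9/1.1)² ≈ 197.3, so 198. Unrounded, the result is 186.

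Both figures reproduce at an unsplit two-sided 0.05 (weight with the rounded difference). Neither contains an adjustment for two outcomes.

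**Step 2. Either outcome suffices**

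With independent tests, P(at least one false significant result) = 1 − 0.95² = 9.75%. In the favourable direction only, it is 1 − 0.975² = 4.94%. Correlated values come from the bivariate normal distribution:

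| ρ (assumed) | At least one, two-sided | At least one, favouring SRA+G |
|---|---|---|
| 0 | 9.75% | 4.9% |
| 0.3 | 9.5% | 4.8% |
| 0.5 | 9.1% | 4.5% |
| 0.7 | 8.4% | 4.2% |
| 0.9 | 7.0% | 3.5% |

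For a single test the corresponding values are 5% and 2.5%.

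**Step 3. Both outcomes required**
- Error when both nulls are true: 0.05² = 0.25% at ρ = 0, rising to 0.9% at ρ = 0.5. When only one null is true, it is at most 5%.
- Power with 80% for each outcome: 0.8 × 0.8 = 64% at ρ = 0, 67% at ρ = 0.3 and 69% at ρ = 0.5.

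**Step 4. Effect of splitting alpha at the stated sizes**

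Power = Φ(δ/(SD·√(2/n)) − 2.241) at two-sided 0.025.
- HOMA-IR, 253 per group: Φ(2.812 − 2.241) ≈ 0.716 (0.713 by the t test).
- Weight, 198 per group, δ = 1.1: Φ(2.806 − 2.241) ≈ 0.714.

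Keeping 80% at 0.025 would need 305 and 239 per group.

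**The case against.** The strongest reply is that this is a condensed article. A success rule is often placed in the full protocol or the statistical analysis plan, neither of which is shown, and separate models at full alpha are compatible with valid procedures: requiring both, or testing in a fixed sequence. That stands to this extent: silence alone would not be a finding, and no single sentence in the article is false. But the article does more than stay silent. It words the primary hypothesis in two incompatible ways and fixes sample sizes on unsplit alpha. A later rule that split alpha or required both outcomes would leave the power of the primary claim below the 80% used for sizing. A fixed sequence would preserve it only for the outcome tested first.

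Three stronger readings are tempting and are not supported.

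- *That the trial's false-positive rate is 9-10%.* Without a rule the rate is undetermined. That range follows only if either outcome suffices and ρ is no more than about 0.5, and it counts errors in both directions although the hypothesis is directional.
- *That the article breaks its own stated 5% and 80%.* Both appear only inside each outcome's own calculation. No study-wide error rate or joint power is declared.
- *That joint power is lower still because weight is analysed only in overweight and obese patients.* A reader might apply the county shares under Settings, eligibility, and recruitment (30% + 34% = 64%) to 253 and get about 162 per group. Those shares describe county residents, not the study sample, so no such figure is used here.

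**Conclusion.** The point holds as a conditional one. Under either reading of the primary hypothesis, one of the two per-outcome design figures does not carry over to the primary claim. If either outcome suffices, error is 9.1-9.75% two-sided at ρ from 0 to 0.5 and still 7.0% at ρ = 0.9; for false claims of benefit alone it remains nearly double that of a single test at ρ up to 0.5. If both are required, error is controlled and joint power is 64-69% over the same range of ρ.

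These results rest on assumed correlations, on 1:1 allocation and, for joint power, on each outcome actually having 80%. Analysing weight in a subset would tend to lower the correlation, towards the upper end of the error range and the lower end of the power range.

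**What to change.** In Analyses, before any results are known, state one rule for the primary claim that controls familywise error at two-sided 5%. Two suitable choices are:

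- **Fixed sequence.** Test one outcome at two-sided 0.05, and the other at 0.05 only if the first is significant. The sponsor should choose the order, since the article ranks neither outcome. Testing HOMA-IR first keeps the calculation of 253 per group intact. Cost: the second outcome cannot be formally claimed if the first fails. Power to claim both is 64-69% if each has 80%.
- **Holm across the two outcomes.** No order is needed. Cost: power for HOMA-IR at the first-step level of 0.025 is about 71% at 253 per group. This is a floor, because HOMA-IR is tested at 0.05 once weight has passed at 0.025.

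Make the wording of the primary hypothesis agree with the rule, and restate power under it in Power and sample size considerations, saying that the 0.05 and 80% there are per outcome and that HOMA-IR is tested two-sided. The sample size can stay as it is. The change is to wording only and adds no patients or measurements.

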**Figure 1 F1:**
[figure not shown]
**Study flow**.

Participants are also asked to complete four study encounters over 13 months: In-person visits at *baseline *and for *risk counseling *(approximately 4-6 weeks after baseline), a remote *3-month survey *(i.e., 3 months after risk counseling), and a *12-month *end-of-study visit. Height and weight (to calculate BMI), waist circumference, fasting plasma glucose and fasting insulin levels are measured at baseline and 12 months. Buccal swabs for DNA collection are obtained from all participants interested in genetic risk testing at the baseline visit. Surveys completed at each encounter will be used to track patients' behavioral and emotional responses to diabetes risk information over time, including perceptions of personal risk for type 2 diabetes. Primary outcomes are changes in insulin resistance and weight; secondary outcomes are changes in diet, physical activity, and waist circumference.

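### The mediation plan seeks a partial-or-full verdict that the sample size cannot support, and states no baseline control for the mediator, perceived risk

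*Protocol article*

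**What the plan says.** The Analyses section of the protocol article sets out the mechanism test: hierarchical regressions are to show whether the arm's effect on 12-month HOMA-IR and body weight "is partially or fully accounted for by perceived risk at 3 months". It thereby names the technique, the mediator, the two outcomes and the form of the conclusion. It gives no criterion for full as against partial, and no interval for the indirect or direct effect.

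The main arm-comparison models in the same section take "arm, clinic site, and baseline patient characteristics as explanatory and control variables". The list is not repeated for the mediation models, and the baseline characteristics are not itemised. Baseline control is described for outcomes: "Residualized change scores (controlling for baseline values) will be used for 3- and 12-month outcome variables". Perceived personal risk is listed elsewhere, under Process Measures.

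The Overview (text under Figure 1) says that surveys at each encounter follow participants' responses over time, "including perceptions of personal risk for type 2 diabetes". Baseline is one of the four encounters, so a baseline value of the mediator is to be expected.

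**The concern.** This is the trial's one test of its hypothesised mechanism, which both the conceptual framework and the Discussion rely on. Two different things can go wrong.

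- **The verdict.** A direct effect that fails to reach significance is not thereby shown to be zero. In a trial sized only for the total effect, a real and dominant direct effect will often be non-significant once the mediator is in the model. A categorical conclusion then invites a claim that perceived risk explains everything.
- **The mediator-outcome path.** Randomisation protects the effect of arm on perceived risk. It does not protect the association of perceived risk with the outcome. People who already saw themselves as at high risk at baseline will tend to do so at 3 months, and they may differ in later weight or insulin resistance for reasons unrelated to the intervention. The Analyses section itself predicts that perceived risk will go with behaviour change whatever the group assignment.

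**Working it through.** **1. The plan's own figure.** Inputs from Power and sample size considerations: "participants in the SRA+G arm will be able to lower HOMA-IR by 0.5 over the course of a year", against a mean change of zero in the SRA arm; "Mean baseline HOMA-IR is estimated to be 2.5 with a standard deviation near 2.0"; two-sided alpha 0.05 and 80% power.

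n per arm = 2 × (1.960 + 0.842)² × (2.0/0.5)² = 2 × 7.85 × 16 ≈ 251.2, so 252. The exact noncentral-t calculation gives 253, the stated figure. The standardised total effect is 0.5/2.0 = 0.25.

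For weight, the target is 2/3 × 1.7 = 1.13 percentage points with SD 3.9, a standardised effect of 0.29, at the stated 198 per arm.

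**2. Power for the direct effect.** Power ≈ Φ(s × d × √(n/2) − 1.96), where s is the share of the total effect that is direct and d the standardised total effect. The shares are assumptions.

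| Direct share s | HOMA-IR: s × 0.25 × √126.5 | Power | Weight: s × 0.2906 × √99 | Power |
|---|---|---|---|---|
| 100% | 2.81 | 80% | 2.89 | 82% |
| 80% | 2.25 | 61% | 2.31 | 64% |
| 70% | 1.97 | 50% | 2.02 | 53% |
| 60% | 1.69 | 39% | 1.74 | 41% |

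**3. How often full mediation would be declared.** Simulation, 4,000 trials per scenario, at 198 per arm (d = 0.29) and 253 per arm (d = 0.25).

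Assumed rule: full mediation is declared when the total effect, the arm-to-mediator path and the mediator-to-outcome path are each significant at 0.05 and the direct effect is not. Assumed effect of arm on perceived risk: 0.3 to 0.5 SD. In the scenarios below, baseline perceived risk has no effect of its own on the outcome.

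| True direct share | Declared full, all trials | Direct effect non-significant, among trials with a significant total effect |
|---|---|---|
| 80% | 15-18% | 22-27% |
| 70% | 24-32% | 33-41% |
| 60% | 34-43% | 44-53% |

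Adding baseline perceived risk to the models leaves the all-trials rates essentially unchanged (15-18%, 25-31% and 34-43%). The false label is a power problem, not a result of leaving out the baseline value.

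**4. Omitting baseline perceived risk.** Assumptions: variables in SD units; effects coded so that positive means benefit; correlation of 0.6 between baseline and 3-month perceived risk; direct effect g of baseline perceived risk on the outcome of +0.2 or −0.2; true mediated share 30%.

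Without the baseline term, the mediator coefficient is shifted by 0.6 × g = ±0.12. The indirect effect is shifted by a × 0.12, where a is the arm effect on perceived risk, and the estimated share by that amount divided by d.

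- HOMA-IR, a = 0.3: 0.036/0.25 = 0.144, so 44% or 16%.
- HOMA-IR, a = 0.5: 0.060/0.25 = 0.240, so 54% or 6%.
- Weight, a = 0.3: 0.036/0.29 = 0.124, so 42% or 18%.
- Weight, a = 0.5: 0.060/0.29 = 0.207, so 51% or 9%.

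The simulation agrees to within a percentage point: 42-54% for g = +0.2 and 6-17% for g = −0.2 when the baseline is omitted, and about 30% in both cases when it is included.

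**The case against.** Most of the case on the other side is sound, and it sets the size of this point.

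- **The significance rule is not in the article.** The text says hierarchical regression and gives no rule that a lost significance means full mediation. This stands, and the percentages in step 3 depend on that reading. But the article does announce a partial-or-full conclusion and offers no other criterion. The power figures in step 2 do not need the rule.
- **The indirect effect is already obtainable.** In nested linear models on the same patients and covariates, the fall in the arm coefficient equals the product-of-coefficients estimate. This stands: the plan does not lack a point estimate. The choice of interval method could also be left to a fuller document. What the article does fix is the categorical verdict.
- **Baseline perceived risk is unnamed, not excluded.** It could be among the unspecified baseline characteristics, or be listed in a document not shown. This stands, so the second weakness is conditional. The article nevertheless states baseline control for the outcomes and not for the mediator.

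A reader might also infer that the plan inflates the indirect effect, or that the missing baseline value is what produces false full-mediation claims. The documents support neither. The bias follows the sign of the baseline association. If high perceived risk marks people with worse metabolic prospects, mediation would be understated and, with 70% direct, full mediation declared in only 2-14% of trials. The false label persists after baseline adjustment.

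**Conclusion.** The point holds as two separate and limited weaknesses.

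- **A partial-or-full verdict is not supportable at these sample sizes.** A direct effect that is 70% of the planned HOMA-IR effect has only about even odds of being detected. Under a significance reading, the mechanism would be called full in about a quarter to a third of trials at that share. These figures rest on the planned effect being true, on the assumed direct shares and arm-to-mediator effects, and on the inferred rule.
- **The mediator-outcome path is exposed to confounding if baseline perceived risk is prognostic and left out.** The size and sign of the bias are unknown, because the article gives no correlation or prognostic strength for it. The ranges above only show that the bias could be material.

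It would go too far to say that the plan will mislabel its mechanism. Nothing here touches the randomised comparison of arms, the sample size or the data collected. The change is still worth making, because it improves the trial's only mechanism test at almost no cost.

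**What to change.** Restate the mediation analysis as two linear models with a common set of baseline terms:

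1. 3-month perceived risk on arm, baseline perceived risk, baseline value of the outcome, clinic site and the chosen covariates.
2. 12-month outcome on arm, 3-month perceived risk and the same baseline terms.

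Report the indirect effect (product of the arm coefficient in model 1 and the perceived-risk coefficient in model 2) and the direct effect (arm coefficient in model 2), each with a bootstrap 95% confidence interval. Remove the partial-or-full conclusion. Confirm in the text that perceived risk is measured at baseline.

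The baseline term deals with the confounding by prior risk perception. The intervals, and the absence of a verdict, deal with the labelling problem. Neither substitutes for the other. The cost is a change of wording and minor analysis work, with no new data if the baseline survey carries the item as the Overview indicates.
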